### Recruitment and enrollment

Recruitment began at the end of July 2020. Due to the COVID-19 pandemic, elective surgeries were suspended in the meantime, complicating recruitment, which is currently ongoing. The anticipated termination of the trial is at the end of March 2023. Since the trial begins only upon admission to the hospital and no intervention appointments are scheduled before that time, no changes in implementation were necessary during the COVID-19 pandemic. Cardiac valve patients on waiting lists in heart surgery centers are screened. To generate generalizable outcomes and consider the internal validity simultaneously, the following in- and exclusion criteria were created:

Inclusion criteria are:

•Scheduled surgery of aortic valve and/or mitral valve (minimally invasive or open heart surgery),•Age ≥ 18 years,•Fluency in German and•Capability to informed consent.

Exclusion criteria are:

•Comorbid medical/psychiatric condition that causes more extensive disability than the coronary condition,•Participation in other studies, e.g., PSY-HEART II; in agreement with the coordinating investigator, a patient can participate in cardiovascular studies if this does not interfere with the main study,•Emergency surgery and•Transcatheter aortic valve implantation (TAVI) procedure.

Cardiac valve patients on waiting lists of the heart surgery centers in Marburg and Gießen who fulfill the inclusion criteria receive an information brochure about the study with their standard letter confirming the surgery date via post. Patients interested in participating in the study contact the study coordinators by phone or by a response letter. In a first telephone call, the study coordinators answer questions and schedule the study participation for interested patients on the day of their hospital admission. The patient information is sent home to interested patients so they can read it at their own pace. On the day of admission, a physician or a psychologist talk about the patient information with each patient, and patients will have an opportunity to ask questions about the study before providing verbal and written consent to the study.

### Assessment

Patients answer questionnaires at four points of time: at baseline on the day of admission (T0a, approx. 20–25 min), after the intervention (EXPECT)/after waiting time in the evening of hospital admission (SOC) (T0b, approx. 5–10 min), 4 to 6 days after surgery (T1, approx. 10–15 min) and 3 months after surgery (T2, approx. 10–15 min). Table 2 shows the applied questionnaires, case report forms, and biological parameters.

**TABLE 2 T2:** Overview of assessment.

Measurement	T0a: Baseline	T0b: Pre-surgery	T1: Post-surgery	T2: Follow-up
**Questionnaires**				
Illness-related disability (PDI)	X		X	X
Health-related quality of life (MLHFQ)	X		X	X
Expected illness-related disability (PDI-E)	X	X	X	X
Quality of life (SF-12)	X		X	X
Illness beliefs (B-IPQ)	X	X	X	X
Expected illness beliefs (IPQ-E)	X		X	X
Situational cognitive valuations (PASA)	X	X	X	
Preoperative anxiety level and information requirement (APAIS)	X	X		
Anxiety (GAD-7)	X		X	X
Depression (PHQ-9)	X		X	X
Dispositional optimism (LOT-R)	X		X	X
Personality (BFI-10)	X			
Self-stigma	X			
Experience with previous surgeries	X			
Demographics (e.g., age, gender)	X			
Relationship	X			
Interest in/Satisfaction with the intervention	X	X		X
Complications				X
Rehabilitation				X
Conversations with other patients				X
**Case report form (CRF)**				
Blood pressure	X		X	
Planned surgical procedure	X			
Realized surgical procedure			X	
Previous surgeries	X			
BMI	X			
Left ventricular ejection fraction (LVEF)	X		X	
NYHA score	X		X	
EuroSCORE II	X		X	
STS-score	X		X	
Smoking	X			
Clinical data (e.g., duration of surgery, hospital stay, Intensive Care Unit)			X	
Complications			X	
**Biological parameters**				
Inflammatory processes (CRP)	X		X	
Platelets and leukocytes	X		X	

PDI, Pain Disability Index (38); MLHFQ, Minnesota Living with Heart Failure Questionnaire (39, 40); PDI-E, Pain disability index-expectation (26); SF-12, short-form health survey (41); B-IPQ, brief-illness-perception questionnaire (42); IPQ-E, expected illness-perception questionnaire (IPQ-R) (26); PASA, primary appraisal, secondary appraisal (43); APAIS, amsterdam preoperative anxiety and information scale (44, 45); GAD-7, generalized anxiety disorder scale (46); PHQ-9, patient health questionnaire (47); LOT-R, revised life orientation test (48, 49); BFI-10, big five inventory (50); Self-stigma (51); NYHA, New York Heart Association Class (52); EuroSCORE II, European System for Cardiac Operative Risk Evaluation (53); STS-score, society-of-thoracic-surgeons-score (54, 55).

Questionnaires completed during the time in the hospital are personally handed out to the patients by the study staff. The T2 questionnaire is sent home to the study participants. Here, patients will be asked to complete the questionnaire and to contact study staff if they have any questions. To increase responses to all questions and avoid missings, patients receive an explanation letter on how to complete the questionnaire along with the T2 questionnaire. The completed questionnaire can be sent back to the study team in a return envelope. If patients have not returned questionnaires after 2 to 4 weeks, they will be contacted by telephone to clarify possible questions and asked to respond.

### Random allocation

After baseline assessment, the patients are randomized to the intervention group (EXPECT) or the control group (SOC). Therefore, the interventionist opens a prepared, concealed envelope to allocate a patient. The randomization result was prepared in this envelope by a student assistant who was not involved in the study. The interventionists and the patients do not know the randomization result before the envelope is unclosed. Randomization was done as block randomization with a balanced allocation ratio (1:1) using WINPEPI (56). Two prestratifications were considered: The study center (Marburg or Giessen) and the scheduled type of surgery (minimally invasive or open heart surgery).

The interventionists will inform the patients about the group they are randomly assigned to. The medical staff will not receive any information about the group a patient is allocated to and therefore be blind regarding group assignments. The intervention group receives a preoperative psychological intervention to optimize expectations and standard of care. The control group receives the standard of care only.

### Psychological intervention

For an overview of the implementation of the intervention, please see the intervention schedule (Figure 2). By default, the intervention (EXPECT) takes place on the day of hospital admission. It lasts approximately 30–40 min. Additionally, two booster calls are implemented 4 and 8 weeks after surgery (10–15 min). In case of short-dated deferrals of surgeries for more than 14 days, one additional booster call is implemented.

**FIGURE 2 F2:**
[figure not shown]
Intervention schedule for EXPECT [adapted from Laferton et al. (26), Salzmann et al. (57)].

The EXPECT intervention is performed by one of four trained psychology students shortly before graduating based on an intervention manual. The same person conducts the entire intervention of one patient. The intervention sessions are videotaped and supervised for verification of manual fidelity. Each patient in the intervention group receives a booklet with information material and worksheets to remember discussed contents.

Content and procedure are based on the EXPECT intervention of the PSY-HEART I-trial [for more details, please see Rief et al. (21), Laferton et al. (26), Salzmann et al. (30)]. The intervention deals with optimizing individual expectations relating to the surgery and the recovery process since the optimization of positive, realistic expectations as part of placebo effects is expected to improve the recovery process in patients undergoing valvular surgeries. Since expectations have been shown to be a central characteristic of depressive and anxiety symptoms and mental disorders (27), the development and amplification of positive-realistic expectations as well as the correction of dysfunctional expectations and illness beliefs within the intervention should also influence psychological factors such as levels of anxiety or depressive symptoms.

Based on the integrative model of expectations in patients undergoing medical treatment (58), generalized self-efficacy, treatment outcome expectations (benefit expectations), timeline expectations, and personalized outcome expectancy are addressed in the EXPECT intervention. Optimization of expectancy effects refers to two main objectives: First, to optimize positive expectations regarding treatment success and impairment after medical heart valve surgery. Second, the intervention should specifically promote positive expectations about one’s coping skills in case of ordinary but unpleasant concomitant effects and potential aversive events due to the surgical procedure. By optimizing the expectations before surgery, the treatment success and recovery process should be improved.

While performing the intervention, the personal disease model and experienced impairments are first inquired. If necessary, the interventionists supplement or correct the disease model. After that, a list of activities is used for a discussion illustrating which activity can be done at which timepoint after surgery (e.g., go for a walk: in the first 6 weeks after surgery, lawnmowing: 6 weeks after surgery, skydiving: 3 months after surgery). Interventionists and patients identify which activities are some the patient looks forward to in order to optimize the patient’s benefit and timeline expectations. Next, patients are educated about risk factors and health behavior before an individual health plan is worked out to strengthen the onset and maintenance of health behavior after surgery. This part focuses on personalized outcome expectancy and self-efficacy. Temporary concomitant effects of the surgery are addressed to prepare the patients for them (treatment outcome and timeline expectations). Individual strategies are developed to deal with concomitant effects (e.g., pain or fears). In this manner, patients’ self-efficacy is strengthened. After summarizing the contents at the end of the personal session, the interventionist guides the patients to imagine their “best possible self” (59) for consolidation. The imagination expresses the success of the surgery and the recovery process by visualizing a situation with increased quality of life 3 months after surgery.

Four and eight weeks after surgery, the interventionists contact the patients in the EXPECT group via telephone for booster calls. In these calls, the interventionists and the patients talk about the implementation of activities and health behavior. Strategies that are already used are reinforced. Difficulties in implementation and solution possibilities for these are discussed. The imagination of the best possible self is repeated and refreshed. The number of booster sessions has been increased in the ValvEx trial since data of PSY-HEART I indicated that EXPECT increased personal control expectations before surgery but failed to maintain that boosted level of perceived personal control expectations after the surgery (60).

### Hypotheses

The study aims to examine if a brief preoperative psychological intervention (EXPECT) compared to standard of care (SOC) leads to a lower level of subjectively perceived illness disability 3 months after surgery. Therefore, the hypothesis μ_EXPECT_ = μ_SOC_ (μ = mean change from baseline) is tested with an α-level of 0.05 (two-sided).

### Outcome criteria

Illness-related disability 3 months after surgery is the primary outcome of the study. It is assessed with an adapted version of the Pain Disability Index (PDI) (38). For this questionnaire, representative data from the German population is available (21, 38).

Manipulation check will be assessed by a change in patients’ expectations (PDI-E, IPQ-E) (26). Secondary outcome variables are health-related quality of life [MLHFQ (39, 40), SF-12 (39)], expectations (PDI-E, IPQ-E) (26), illness beliefs (B-IPQ) (42), situational cognitive valuations (PASA) (43), preoperative anxiety level and information requirement (APAIS) (44, 45), anxiety (GAD-7) (46), depression (PHQ-9) (47), dispositional optimism (LOT-R) (48, 50), rehospitalization, length of hospital stay, length of time at intensive care unit, experience with previous surgeries, planned and realized surgery, EURO-Score II (53), STS-Score (54, 55), blood pressure, left ventricular ejection fraction (LVEF), New York Heart Association (NYHA) score (52), complications, inflammatory processes [C-reactive protein (CRP)], platelets and leukocytes and participation in rehabilitation program (e.g., cardio sport group).

### Data analysis

For examination of the primary hypothesis (H0: μ_EXPECT_ = μ_SOC_; H1: μ_EXPECT_ ≠ μ_SOC_), the illness-related disability 3 months after surgery will be analyzed using linear mixed models (baseline-adjusted, patients nested in operation type nested in centers). Main effects for group, time, and group x time will be calculated with primary focus on the difference in treatment effect (difference in mean change between baseline and 3-months follow-up between EXPECT and SOC). In doing so, a fixed significance level of α = 0.05 will be used, and Intention-to-treat-analysis (ITT) will be conducted. The reasons for upcoming missings will be analyzed, and robust maximum likelihood estimation procedures will be applied.

95% confidence intervals will be calculated for the estimation of differences in mean values. Relevant factors such as strata (center, surgery method), baseline characteristics (e.g., age, gender, level of baseline depression and anxiety score) or potential confounding (e.g., differences in interventionists) may also be considered in secondary analyses. The same procedure will be applied for secondary outcomes.

In the PSY-HEART I study, the EXPECT intervention has been shown to have partially different effects for different severities of some outcomes, for example due to the fact that the EXPECT intervention significantly decreased depressive symptoms at 6 months follow-up for patients with high baseline depressive symptoms, but not for patients with low baseline depressive symptoms (60). Therefore, covariate/moderator analyses will be conducted to examine whether the intervention is more effective for specific subgroups in terms of “what works best for whom”.

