## Introduction

Heart disease accounts for nearly 10% of all recorded diagnoses in Germany, with an upward trend (1, 2). Cardiovascular diseases are prevalent globally, with a point prevalence of 523 million cases recorded in 2019, and are the leading cause of death worldwide (1, 3). The number of cardiovascular surgeries is also steadily increasing: Between 2008 and 2018, there has been an increase of 23% (4). In 2019, 36 650 heart valve surgeries were performed in Germany (2). The aim of surgical heart valve intervention, such as aortic or mitral valve surgery, is to recover the function of the heart valve through reconstruction or replacement (5). Valve surgeries significantly improve the odds of survival for affected patients (5, 6). However, despite high survival rates after cardiac surgery, the postoperative recovery is highly variable and often unfavorable: a substantial number of patients still feel restricted after surgery, still experience a high illness-related disability, do not perceive an improvement in quality of life, suffer pain or have increased depression scores that persist or even rise for weeks and months after hospital discharge (6–14).

Besides the surgical trauma itself and physical factors like age or general health condition, preoperative psychological factors also influence the recovery process after cardiac surgery (6). Preoperative expectations, illness beliefs (e.g., preoperative illness and treatment-related beliefs), anxiety, and depressive symptoms influence the recovery process, chances of survival, perceived physical and psychological disability, perceived quality of life, and depressive symptoms after cardiac surgery (13, 15–21). Negative expectations before coronary surgery, such as expectations regarding the outcome, the consequences, and the success of treatment, lead to more complications, worse quality of life, higher illness-related disability, increased depressive symptoms, and a postponed return to work (13, 22–24). Given the impact of expectations and illness beliefs on postoperative outcomes and the possibility that these constructs are specifically modifiable through psychological preparation, there is a need to develop preoperative interventions to improve long-term recovery (12, 25).

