### Study design

The ValvEx-trial is a randomized controlled trial (RCT). It is performed in two centers (the university hospital of Gießen and the university hospital of Marburg). The trial examines the impact of a brief preoperative psychological intervention that aims to optimize expectations (EXPECT) in addition to standard of care compared to standard of care (SOC) only in heart valve patients. The randomization ratio is balanced (1:1). Assessments take place on the day before surgery in the hospital (Baseline, T0a), on the evening before surgery, after the intervention (EXPECT)/after waiting time in the evening of hospital admission (SOC) (T0b), 4 to 6 days after surgery (T1) and 3 months after surgery (T2). Figure 1 shows the calculated study flow-chart, including the participants’ targeted count for each measurement.

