### Sample size and study power

In PSY-HEART I, a large effect (*d* = 0.8) was detected relating to the pre-post comparison of the primary outcome (illness-related disability) in the EXPECT and SOC group (21). Since the intervention is shortened to one preoperative session (and two additional booster sessions after surgery) in ValvEx, a small to medium effect is expected (*d* = 0.2–0.5). Given a power (1 − β) of 0.8 and a significance level of *p* = 0.05, a sample size of *N* = 74 is required to detect the described effect (*d* = 0.3, *f* = 0.15). In due consideration of a drop-out rate amounting to 20% for refusals and terminations of treatment, a recruitment aim of *N* = 88 is intended.

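### Baseline depression, a named influence on postoperative disability measured before randomisation, is left out of the primary model; pre-specifying PHQ-9 could gain modest precision at almost no cost

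*Protocol article*

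**What the plan says.** The Introduction lists several preoperative factors that bear on recovery after cardiac surgery: expectations, illness beliefs, "anxiety, and depressive symptoms influence the recovery process, chances of survival, perceived physical and psychological disability". Perceived illness-related disability, measured with an adapted PDI, is the primary outcome (Outcome criteria).

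Table 2 schedules PHQ-9 at T0a, and Random allocation places randomisation after the baseline assessment. Every randomised patient should therefore have a PHQ-9 score that the allocation cannot have affected.

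The Data analysis section specifies a linear mixed model for the primary outcome, baseline-adjusted, with patients nested in operation type nested in centres. The primary contrast is the difference between arms in mean change from baseline to 3 months. Depression is not in that model. It comes in the next paragraph with the strata, age and gender: "level of baseline depression and anxiety score) or potential confounding (e.g., differences in interventionists) may also be considered in secondary analyses". The same section commits firmly to covariate and moderator analyses, motivated by a finding on baseline depression in the earlier trial.

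On missing data, the section says "The reasons for upcoming missings will be analyzed" and plans robust maximum likelihood estimation.

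**The concern.** The article names an influence on its primary outcome, measures it before randomisation, and then leaves it out of the primary analysis. A pre-randomisation covariate that explains outcome variance beyond baseline PDI narrows the confidence interval for the treatment effect and asks nothing more of patients. The trial is small: the power section plans on 74 analysed patients. What is at stake is some precision in the 3-month contrast. The validity of the test is not in question.

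**Working it through.** **The plan's own sample size.** Inputs: "is tested with an α-level of 0.05 (two-sided" (Hypotheses); "Given a power (1 − β) of 0.8 and a significance level of" 0.05 and "a sample size of *N* = 74 is required to detect the described effect (*d* = 0.3, *f* = 0.15" (Sample size and study power); "The randomization ratio is balanced (1:1" (Study design); PDI at T0a, T1 and T2, so m = 3 (Table 2).

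N = 74 reproduces as a group by time interaction in a repeated-measures ANOVA with correlation ρ = 0.5 and sphericity. Neither is stated, so both are assumptions.

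- Noncentrality: λ = f² × N × m / (1 − ρ) = 0.0225 × 74 × 3 / 0.5 = 9.99
- Degrees of freedom: 2 and (74 − 2) × 2 = 144
- Power: 0.806, and 74 is the smallest even N that reaches 0.80

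**Effect of adding PHQ-9.** Let r be the partial correlation of T0a PHQ-9 with 3-month PDI, given baseline PDI. The model already adjusts for baseline PDI, so only what PHQ-9 explains beyond it counts. The article gives no value for r; 0 to 0.4 is assumed. Taking the analysis as an ANCOVA on 3-month PDI, one further covariate changes the standard error by

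SE ratio = √[(1 − r²) × (N − 4)/(N − 5)]

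The second factor is the price of estimating one more coefficient. With N = 74 it is 70/69 = 1.0145.

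| r | 1 − r² | SE ratio | Change in SE |
|---|---|---|---|
| 0 | 1.00 | 1.007 | +0.7% |
| 0.1 | 0.99 | 1.002 | about 0 |
| 0.2 | 0.96 | 0.987 | −1.3% |
| 0.3 | 0.91 | 0.961 | −3.9% |
| 0.4 | 0.84 | 0.923 | −7.7% |

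Break-even is where 1 − r² = 69/70, so r² = 0.014 and r is about 0.12. The plan also allows for dropout: "In due consideration of a drop-out rate amounting to 20% for refusals and terminations of treatment", with recruitment of 88. A 20% loss from 88 leaves 88 × 0.8 = 70.4. At N = 70 the ratios move by no more than 0.001.

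**In terms of power.** Replacing f by f/√(1 − r²) in the interaction calculation at N = 74 moves power from 0.806 to 0.811, 0.823, 0.844 and 0.873 for r = 0.1, 0.2, 0.3 and 0.4. The N for 80% power goes from 74 to 74, 72, 68 and 62. This charges nothing for the extra parameter and depends on the assumed ρ, so it only indicates size.

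**Missing forms.** A simulation set a true difference of −0.30 SD and about 20% missing 3-month values. It assumed correlations of 0.5 between baseline and 3-month PDI and between baseline PDI and depression, and r of 0.2 or 0.4. The analysis model held baseline PDI only. Where depression affected missingness, the log-odds slope was 0.7 per SD.

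- Same slope in both arms: estimates of −0.301 and −0.298, so no bias.
- Slope in one arm only: −0.322 and −0.340 (EXPECT), −0.277 and −0.261 (SOC), a bias of about 0.02 to 0.04 SD.
- Opposite slopes in the two arms: −0.340 and −0.382, a bias of about 0.04 to 0.08 SD.
- With depression in the model: −0.297 to −0.302 in all these cases.

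**The case against.** The strongest reply is that nothing here is wrong. The article fixes a primary model and puts further covariates in secondary analyses. In a randomised trial, leaving out a prognostic covariate does not invalidate the test, and a final covariate list may sit in an analysis plan that is not shown. This stands as to validity, and it is why the point is an improvement and not an error. It does not remove the point, because the article itself assigns depression to optional secondary work.

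It is also fair that depression is one of four influences named together, that nothing ranks it above the others, and that the gain is assumed and modest: at r of 0.3 or less the standard error falls by at most about 4%.

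Three stronger readings are tempting, and the documents support none of them.

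- A reader might infer that depression drives postoperative disability. The Introduction says only that it is one influence, and gives no size.
- A reader might infer that more depressed patients will return fewer 3-month forms and that the plan ignores this. No section says depression predicts non-return. The plan will examine reasons for missingness, use likelihood methods with PDI also measured at T1, and follow up unreturned forms by telephone. In the simulation, bias arises only if the link between depression and missingness differs between arms. Only EXPECT patients receive booster calls, which makes a difference conceivable, but the documents do not show one.
- A reader might infer that results could guide the choice of primary model. The optional wording governs secondary analyses, and no text lets an adjusted model replace the primary one.

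**Conclusion.** The point holds as an efficiency improvement. PHQ-9 is a pre-randomisation measure of a factor that the article itself calls influential, and the primary model does not use it. For an assumed partial correlation of 0.1 to 0.4 the standard error falls by about 0 to 8%; at zero it rises by 0.7%. The potential gain therefore outweighs the potential loss, but its size is unknown and probably small. The figures rest on the assumed range for r and on an ANCOVA form of the primary model. The primary comparison is valid as it stands.

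**What to change.** Before outcomes are analysed by group, pre-specify T0a PHQ-9, as a continuous score, in the primary model whatever the observed balance between arms. The form depends on a point the article leaves open, namely whether T0a PDI is one of the outcomes:

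- If only post-baseline PDI is modelled, enter PHQ-9 as a covariate alongside baseline PDI and the randomisation strata (centre and scheduled type of surgery).
- If T0a PDI is in the outcome vector, enter PHQ-9 by time. A main effect alone shifts all visits equally and so largely cancels from a change-from-baseline contrast.

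The SE ratios above apply to the first form. In the second, the gain depends on how PHQ-9 relates to change in PDI, for which the article gives no figure either.

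Report the model without PHQ-9 as a sensitivity analysis, and take baseline depression off the list of optional adjustment factors. The planned moderator analyses can stay.

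The cost is a line or two of text and one or two parameters: one for a common PHQ-9 slope in the first form, or two interaction terms, one for each post-baseline visit, beside the main effect in the second. No new data are needed.
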